##### Help-Seeking Intentions

Help-seeking intentions were measured using the General Help-Seeking Questionnaire (GHSQ) [48], to which we added the options *teacher* and *school welfare coordinator/school counselor* to match all sources of help to the items in the Beliefs About Help section. Average scores for the following three categories will be calculated: (1) general help-seeking intentions, (2) help-seeking intentions using informal sources, and (3) help-seeking intentions using formal sources. Higher scores will indicate higher intentions. The GHSQ has good internal consistency and excellent test-retest reliability [48].

##### Help-Seeking Behavior

Help-seeking behavior was assessed by asking whether the participants themselves had experienced a problem similar to the situation in the vignette. If they responded with *yes* or *not sure*, they were asked whether someone has helped them with this problem in the last three months and who this person was: multiple options were allowed. We did not distinguish between whether the help was provided to the participant or whether they sought out the help from this person themselves. The same list of people from the Beliefs About Help section and the GHSQ [24,48] was used with the additional response option *Don’t know for sure*. If the participant indicated their boyfriend or girlfriend and/or a friend had helped them, they were asked what that person did out of the 12 first aid actions and the open-ended option mentioned in the First Aid Intentions section above [28]. This was done in order to assess the first aid skills in youth surrounding the person who had experienced a problem such as that in the vignette.

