**Objective:**

Our aim is to describe the protocol for a study that will test the effectiveness of the program Moving Stories in a Dutch adolescent sample. We hypothesize that adolescents who participate in the program Moving Stories will have better mental health literacy and less stigma regarding depression compared to adolescents in the nonintervention control group at posttest and at 3- and 6-months follow-up. We also expect a positive change in actual help-seeking and first aid behavior at 3- and 6-months follow-up.

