### Objectives

The goal of this paper is to describe the protocol for a study that will test the effectiveness of the program Moving Stories in a Dutch adolescent sample by means of a randomized controlled trial. Our first hypothesis is that adolescents who participate in the Moving Stories program will have better mental health literacy and will endorse fewer stigmatizing attitudes regarding depression than adolescents who do not participate, both directly at posttest and at 3- and 6-months follow-up. Second, we expect a change in help-seeking and first aid behavior. At 3- and 6-months follow-up, we expect that adolescents in the Moving Stories group, compared to the control group, will have sought more help if they were experiencing depressive symptoms or provided increased appropriate first aid if they were in contact with a peer who was experiencing depressive symptoms.

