### Program

Moving Stories is a game-based school program, which consists of three parts: (1) an introduction lesson; (2) a single-player, mobile, 3D video game; and (3) a contact session with someone with lived experience with a depressive disorder. The program targets three components of mental health literacy, specifically regarding depression, namely (1) recognition of when a disorder is developing, (2) knowledge of help-seeking options and treatments available, and (3) first aid skills to support others who are developing a mental disorder or are in a mental health crisis [10]. Moreover, the program aims to decrease stigma around depression among youth. Moving Stories has been developed for high school students and should be offered to an entire class. The program is delivered within one week, making it convenient to incorporate into schools.

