**Figure 4 figure4:**
[figure not shown]
Lisa's house in Moving Stories (screenshot).

After five days of playing, the program finished with a contact session. In this concluding session, the story of the girl in the game was brought into the real world. A trainer with lived experience with depression led the contact session. All trainers have been trained by the Trimbos Institute in telling their story, guiding a discussion about the game, and translating their story and that of the game to specific first aid skills. In the session, the trainer told their own story and used the experiences of the adolescents in the game to discuss five first aid skills the adolescents could go back to when they want to help a friend who might be suffering from depression. These five skills, or action points, in helping a friend were based on content from the teen Mental Health First Aid training [24] and have been translated into Dutch: (1) Look for warning signs, (2) Ask how they are, (3) Listen without judgment—“without judgement” was added specifically to this program, (4) Help them connect with an adult, and (5) Be a friend. During the contact session, adolescents were allowed to ask questions about the game and about the experience of the trainer. To guide the discussion, the trainer used a PowerPoint presentation with predetermined questions that were related to the content of the game and the five action points. A member of the research team was present to make sure that all questions were discussed.

Moving Stories has been developed through a close collaboration between game designers and behavioral scientists using an iterative design process (see Figure 5). This means that multiple prototypes have been tested in pilot studies before the final version was built. All stakeholder groups have been involved during each development phase, including youth, therapists, and teachers. The concept of the game was based on the latest literature and best practice experiences. In total, we ran through five iteration rounds, each with several playtests. Over 200 people played the game before final development.

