**Figure 5 figure5:**
[figure not shown]
Iterative design process for the development of Moving Stories. RCT: randomized controlled trial.

To verify that Moving Stories does not increase depressive symptoms or suicidal ideation in adolescents, the Child Depression Inventory (CDI) [37,38] was administered. At all assessment points, if adolescents had a score on depressive symptoms in the clinical range and/or suicidal intention (CDI>29 and/or a score of 2 on question 9 of the CDI) [37,38], both the parents and adolescent were contacted by phone by a clinically trained member of the research team to inform them of the result and to give advice on where to seek professional help. We follow standard Dutch guidelines, in which we refer adolescents and their parents to the appropriate professional channels of care, where they will receive an assessment and subsequent intake if necessary. No follow-up of this group will be initiated from the research team itself. This procedure was approved by the Research Ethics Committee and complies with Dutch care guidelines. Adolescents who were contacted were not excluded from participating in the study, since that would increase stigma. During analyses, we will check and, if necessary, control for the possible effects of contacting participants and referring them to care.

To make sure that all adolescents who seek help from teachers during the study receive the help that they need, all teachers were provided with an information booklet developed for this study that includes short practical tips on what they can do to help their students. The primary researcher informed the teachers and other professionals involved at the school about the study and the short practical tips at an information session. In addition, teachers had the opportunity to follow an e-learning program on suicidality and depression in youth. This program, called Mental Health Online [39], aims to improve knowledge and self-confidence in people working with youth and has been found to be effective [40]. For this study, the developers of Mental Health Online have added an information page on depression to the program, since the e-learning program mainly discusses suicidality in youth [41] (in Dutch).

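### Hypothesis 2 predicts more help sought, but the item records help received, so a difference between arms cannot be read as more help-seeking

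*Protocol article*

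**What the plan says.** **Hypothesis.** The Objectives section compares the arms at 3 and 6 months and expects that Moving Stories pupils "will have sought more help if they were experiencing depressive symptoms". The Abstract (Objective) puts it more strongly: "We also expect a positive change in actual help-seeking and first aid behavior at 3- and 6-months follow-up".

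**Measure.** Under Help-Seeking Behavior, pupils who report, or are unsure about, a problem like the one in the vignette get the follow-up: "they were asked whether someone has helped them with this problem in the last three months and who this person was". Several helpers may be ticked. The same paragraph states: "We did not distinguish between whether the help was provided to the participant or whether they sought out the help from this person themselves". The GHSQ, under Help-Seeking Intentions, covers intentions only.

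**Program.** The Program section says that Moving Stories "should be offered to an entire class". One of its three literacy targets is "first aid skills to support others who are developing a mental disorder or are in a mental health crisis", and one of the five action points taught in the contact session is "Help them connect with an adult".

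**Limitations.** The Discussion covers contamination, unobserved conversations, self-report and the lack of objective behavioural measures. It limits conclusions about first aid behaviour. It does not mention the difference between sought and received help.

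**The concern.** The hypothesis is about something the pupil does. The item records an event that may be wholly someone else's doing.

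This would be ordinary measurement error if unsolicited help were equally common in both arms. The program gives a reason why it may not be. If it works as intended, the classmates of a struggling intervention pupil become readier to step in and to involve an adult, while the classmates of a control pupil do not. The outcome labelled help-seeking could then rise in the intervention arm without any pupil seeking more help.

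The article presents actual help-seeking as a gap that existing programs leave open (Abstract, Background; Introduction, on existing interventions). A difference on this item, reported under its present name, would be taken as evidence on that gap. The caveat appears in the definition of the measure but does not reach the hypothesis or the limitations.

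**Working it through.** **No plan figure to reproduce.** The documents give no expected rate, effect size or power for this outcome. The sample size of 180 rests on mental health literacy and stigma and does not bear on the point.

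**Step 1: hypothesis and item side by side.**

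| Situation of a pupil with a problem | Counts as help sought | Counts on the item |
|---|---|---|
| Asks for help and gets it | yes | yes |
| Asks for help and does not get it | yes | no |
| Does not ask, but someone helps | no | yes |
| Neither asks nor is helped | no | no |

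The two disagree in the middle rows. The third row is where the program may act directly, through trained classmates.

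**Step 2: how far the item can move with no change in seeking.** All rates here are assumed. Let *s* be the probability that a pupil sought and obtained help, and *u* the probability of unsolicited help, taken as independent of *s*. Then

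P(helped) = 1 − (1 − s)(1 − u).

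With *s* equal in both arms, the difference between arms is (1 − s)(u₁ − u₀). Take u₀ = 0.20 in controls:

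| s (both arms) | u₁ = 0.30 | u₁ = 0.40 | u₁ = 0.50 |
|---|---|---|---|
| 0.20 | 0.80 × 0.10 = 0.08 | 0.80 × 0.20 = 0.16 | 0.80 × 0.30 = 0.24 |
| 0.30 | 0.70 × 0.10 = 0.07 | 0.70 × 0.20 = 0.14 | 0.70 × 0.30 = 0.21 |
| 0.40 | 0.60 × 0.10 = 0.06 | 0.60 × 0.20 = 0.12 | 0.60 × 0.30 = 0.18 |

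The item shows a difference of 6 to 24 percentage points while the effect on seeking is zero.

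**Step 3: the item cannot tell the two explanations apart.** Start from s = 0.20 and u = 0.20, so P(helped) = 1 − 0.80 × 0.80 = 0.36.

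- Raise seeking to 0.30 and leave unsolicited help alone: 1 − 0.70 × 0.80 = 0.44.
- Raise unsolicited help to 0.30 and leave seeking alone: 1 − 0.80 × 0.70 = 0.44.

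The result is the same 8-point rise.

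**Step 4: the error can also run the other way.** In the first case of step 3, a true 10-point rise in seeking shows as 8 points, because some of those pupils would have been helped anyway. If only a fraction *q* of those who seek help obtain it, the rise shrinks to 8*q* points.

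**The case against.** **The authors disclose it.** They do, in the definition of the outcome. Disclosure there does not change what the hypothesis claims, and the limitations do not take it up.

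**The source of help is recorded.** Pupils name who helped. If a friend or partner did, they also report which of the 12 first aid actions that person took. This describes the peer route, and a reader might infer that splitting formal from informal sources would isolate help-seeking. It would not: pupils are taught to bring in an adult, so help from an adult may also have been set in motion by a friend, and help from a friend may have been asked for.

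**The illustration is not evidence of a false-positive result.** This stands. Suppose 30 pupils per arm report a problem, 40% seek help in both arms, and unsolicited help reaches 25% of the rest in the intervention arm against 10% in controls. The helped rates are 0.40 + 0.60 × 0.25 = 0.55 and 0.40 + 0.60 × 0.10 = 0.46. The standard error is √(0.55 × 0.45/30 + 0.46 × 0.54/30) ≈ 0.129, so z ≈ 0.70 and p ≈ 0.48 before clustering. A bias of that size would usually not reach significance. The problem is what the estimate means, and that does not depend on significance.

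**Two stronger readings are not supported.**

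- A reader might infer that the study's own phone calls after a high CDI score bias the comparison, since "both the parents and adolescent were contacted by phone by a clinically trained member of the research team". The Procedure section applies one rule at every assessment without regard to condition, and it already plans to check for effects of the contact and control for them if needed.
- A reader might infer that the two halves of Hypothesis 2, seeking and giving help, are confounded with each other. Giving help is measured separately, from the giver, under First Aid Behavior. Any spill-over runs one way, from peers' giving into the helped item.

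**Conclusion.** The point holds as a mismatch between hypothesis and measure. Hypothesis 2 is worded as help sought; the item records help received, includes unsolicited help and omits help sought without success. Because the program itself trains classmates to offer help, the unsolicited part may differ by arm, and a difference on this item does not support a statement about actual help-seeking in either direction.

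The size of the bias is unknown from the documents. The 6 to 24 points are an illustration that rests on assumed rates, on independence of sought and unsolicited help, and on some of the helpers being trained classmates. It would be too much to say that a positive result *would* be an artefact; the documents show only that this item cannot exclude it. The measurement of first aid behaviour and the literacy and stigma outcomes are untouched.

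**What to change.** - Reword the help-seeking half of Hypothesis 2, the outcome name and the conclusions as *help received*.
- Carry the caveat from the outcome definition into the limitations. Add that help sought but not obtained is missed, and that trained classmates may raise unsolicited help in the intervention arm.
- Claim no change in actual help-seeking from this item. The GHSQ can support statements about intentions only.
- Report help received by source (peer, parent, formal), using the list already collected, as a descriptive or sensitivity analysis. State that it does not separate sought from offered help.

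The Results section says that the last follow-up data were collected in December 2018, so an item on who took the initiative can no longer be added for this trial. The changes need only rewording and a tabulation of existing responses. The price is a more modest behavioural claim.

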##### Evaluation of Moving Stories

During posttest, participants in the intervention group were asked to evaluate the program Moving Stories across seven items using a 5-point scale from 1 (totally disagree) to 5 (totally agree); for example, “How much do you agree with the following statement? I would like to play the game another time to get a better score.” To distinguish between the different components of the program and the study (ie, game, evaluation session, and research), the participants were also asked which of the components they would recommend to a friend if they had the opportunity to participate in the study over the next year.

##### Contamination Check

To check for possible contamination effects due to the within-school randomization, the participants in the control group were asked at 6-months follow-up whether they had heard of the game Moving Stories and, if so, whether they had played it. If they indicated they had played it, they were asked on what platform they did so.

### Sample Size

The sample size was based on the expected difference (Cohen *d*=0.40) between the intervention and control condition for mental health literacy and stigma at 3-months follow-up, based on Perry et al [23]. We performed a power analysis using Stata version 14.2 (StataCorp) [49], assuming baseline-adjusted regression analyses (alpha=.05; beta=.20). Our provisional estimates for the correlations between pre- and posttest and between posttest and 3-months follow-up are .50. A coefficient of variation of .19 (estimated mean cluster size=18; estimated cluster size range=11-25 [50]) and an intracluster correlation coefficient of .02 [23] lead to a design effect of 1.35. Taking into account the design effect, we calculated that we need 3.75 classes per condition to show the expected effect, rounding up to four classes per condition, with 18 adolescents per class. To adjust for a *t* distribution [51], we added one class per condition, resulting in five classes (ie, 90 adolescents) per condition and a total necessary sample size of 180. Since we will perform the analyses according to the intention-to-treat principle, dropout was not taken into account.

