**Methods:**

Moving Stories has been developed by a professional game design company in collaboration with researchers and relevant stakeholders. The effectiveness of Moving Stories will be tested through a randomized controlled trial with two conditions: Moving Stories versus control. Participants will fill in questionnaires at pretest, posttest, and 3- and 6-months follow-up. Our power analysis showed a required sample size of 180 adolescents.

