### Statistical Analyses

Descriptive statistics will be calculated for all variables of interest (eg, knowledge of first aid, stigma, and help-seeking intentions). In order to assess whether randomization results in similar groups, we will examine whether there are differences between the two conditions on relevant covariates (ie, sex, age, educational level, ethnicity, gaming behavior, and depressive symptoms) using *t* tests for the continuous variables and chi-square tests for the categorical variables. Variables that are distributed differently between the two conditions will be entered as control variables in all models testing the effects of the conditions.

We will perform our analyses according to the intention-to-treat principle, meaning we will include all children who filled in the pretest questionnaires in the analyses to test the study hypotheses. We will control for clustered data because children are nested within classes. We will use Mplus version 8 (Muthén & Muthén ) [52] for the analyses, since it has special features to deal with missing data. It also allows for analyzing complex data while controlling for clustering. To test whether children in the experimental condition have shown an increase in mental health literacy and a decrease in stigma at 3- and 6-months follow-up, compared to the control condition, regression analyses will be conducted. Both the effect sizes and the confidence intervals will be reported. Open-ended questions will be analyzed exploratively and indicatively where necessary.

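### The 3.75 classes per condition do not follow from the stated 3-month target: with five classes per arm, power for d=0.40 is about 65–76% if the pretest-to-3-month correlation is .50, not 80%

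*Protocol article*

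**What the plan says.** The Sample Size section (protocol article, Methods) takes Cohen's d of 0.40 as its target, and the comparison it sizes is "between the intervention and control condition for mental health literacy and stigma at 3-months follow-up". The method is given as "assuming baseline-adjusted regression analyses (alpha=.05; beta=.20". Two correlations are supplied, pretest with posttest and "between posttest and 3-months follow-up are .50". The pretest-to-3-month correlation is not given.

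A mean class size of 18, a coefficient of variation of .19 and an intracluster correlation of .02 give a design effect of 1.35. The section then reports "we calculated that we need 3.75 classes per condition to show the expected effect, rounding up to four classes per condition". One further class per condition is added for the t distribution, making five classes or 90 pupils per condition. Dropout is not allowed for. The Abstract carries the result forward: "Our power analysis showed a required sample size of 180 adolescents".

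The Statistical Analyses section plans regression to test "an increase in mental health literacy and a decrease in stigma at 3- and 6-months follow-up". Neither it nor the Objectives section names an outcome averaged over time points.

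**The concern.** The target is one time point, but the number of classes looks too small for it. A baseline correlated .50 with a single follow-up removes a quarter of the outcome variance, whereas the printed figure needs half removed. In addition, the posttest-to-3-month correlation plays no part in a regression of the 3-month score on pretest, so its presence suggests that a different quantity was sized.

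If so, 180 pupils is not the number required for 80% power at 3 months. The chance of missing a true d=0.40 would be nearer one in three or one in four than one in five, and a non-significant 3-month result would be weaker evidence against the planned effect than the stated power implies.

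**Working it through.** **Inputs from the Sample Size section.** d=0.40; alpha .05 (sidedness not stated; two-sided reproduces the figure); power .80; correlations .50; mean class size 18; CV .19; ICC .02; five classes per condition; no dropout.

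**Assumed input.** Pretest-to-3-month correlation r=.50, with a range shown below.

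**Step 1: design effect.** 1 + ((1 + .19²) × 18 − 1) × .02 = 1 + 17.65 × .02 = 1.353. The stated 1.35 is right.

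**Step 2: unadjusted size.** 2 × (1.960 + 0.842)² / 0.40² = 98.1 per arm.

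**Step 3: reproducing 3.75.** With one baseline and p follow-ups, the ANCOVA variance factor is (1 + (p − 1) × r_FF)/p − r_BF², where r_FF is the correlation between follow-ups and r_BF that of baseline with follow-up. For p=2 and all correlations .50, it is (1.5)/2 − .25 = 0.50. Then 98.1 × 0.50 = 49.06, rounded up to 50, and 50 × 1.35 / 18 = 3.75, an exact match. Without rounding up to 50 it would be 3.68.

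Alternatives, each rounded up to whole pupils:

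| Calculation | Factor | Classes per condition |
|---|---|---|
| ANCOVA, one follow-up | 0.75 | 5.55 |
| ANCOVA, three follow-ups | 0.417 | 3.08 |
| Two baselines, one follow-up | 0.667 | 4.95 |
| Single change score, or no adjustment | 1 | 7.43 |
| One-sided alpha, factor 0.75 / 0.667 / 0.50 | – | 4.35 / 3.90 / 2.93 |
| 1 − r used in place of 1 − r² | 0.50 | 3.75 |

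Only a factor of 0.50 with two-sided alpha gives 3.75, and two routes lead to it: averaging two follow-ups, or a slip of 1 − r for 1 − r².

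**Step 4: the stated target.** For one follow-up the factor is 1 − .50² = 0.75. Then 98.1 × 0.75 = 73.6, rounded up to 74; 74 × 1.35 / 18 = 5.55, rounded up to 6. The plan's extra class makes 7 per condition, or 7 × 18 × 2 = 252 pupils. Power there is 82.5% (t, 12 df).

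**Step 5: power with five classes.** Effective size per arm is 90 / 1.35 = 66.7. The standard error in SD units is √(2 × 0.75 / 66.7) = 0.150, and 0.40 / 0.150 = 2.667.
- Noncentral t with 2 × 5 − 2 = 8 df: 64.8%.
- Normal reference: Φ(2.667 − 1.960) = 76.0%.
- Factor 0.50 for comparison: 0.40 / √(1/66.7) = 3.266, giving 81.5% (t) or 90.4% (normal).
- Effect detectable with 80% power at factor 0.75: d=0.48 (t), or 2.802 × 0.150 = 0.42 (normal).

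**Step 6: range for the unstated correlation** (five classes of 18 per arm, d=0.40, factor 1 − r²).

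| r | Factor | Power, t 8 df | Power, normal |
|---|---|---|---|
| .30 | 0.91 | 57% | 68% |
| .50 | 0.75 | 65% | 76% |
| .60 | 0.64 | 72% | 82% |
| .70 | 0.51 | 81% | 90% |

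**The case against.** Four objections deserve an answer.

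**The key correlation is not stated.** This stands. The factor of 0.75 needs the pretest-to-3-month correlation, and the two correlations given are themselves called provisional. A single power figure would be firmer than the document allows. At about .70 the t-based 80% is reached; with a normal reference it is reached between .50 and .60. Nothing in the section, however, claims a correlation above .50, and a lower value makes the shortfall worse.

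**The t reference with 8 df is the pessimistic choice.** This stands in part. No degrees of freedom are given, and the Statistical Analyses section names clustered regression in Mplus without a reference distribution. But the Sample Size section adds a class precisely to allow for a t distribution, and the same t test gives 81.5% under factor 0.50, so it is the like-for-like comparison. The normal figure of 76% is also below 80%.

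**The cause is inferred.** This stands. A reader might conclude that the authors sized the mean of posttest and 3 months. The supplied posttest-to-3-month correlation makes that likely, but the text does not mention averaging, and 1 − r for 1 − r² gives the same number. A reader might likewise infer separate models at each time point; the Statistical Analyses section says only that regression will be used. The finding depends on neither inference, since the section sizes the 3-month difference in its own words.

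**Nothing can now be changed in conduct, and intervals will be reported.** This is true. Estimates are not biased, and confidence intervals will show imprecision directly. It limits the consequence but does not make the stated requirement correct.

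**Conclusion.** Wrong as written. The 3.75 classes need a variance factor of 0.50, whereas the stated target of one follow-up with baseline adjustment gives 0.75 when the pretest-to-3-month correlation is .50. On that assumption, and with ICC .02, design effect 1.35, five classes of 18 per arm and no dropout, power for d=0.40 at 3 months is about 65% (t, 8 df) to 76% (normal reference). The effect detectable with 80% power is d=0.48 or 0.42 respectively. Any dropout would lower these powers.

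The documents do not support a flat statement that power is 65%, because the correlation and the reference distribution are both unstated. Nor do they establish that an averaged endpoint was intended.

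**What to change.** In the Sample Size section, replace the statement that 3.75 classes (and so 180 pupils) suffice for 80% power at 3 months. State the assumed pretest-to-3-month correlation and report that, at .50, ten classes of 18 give about 65% (t, 8 df) to 76% (normal) power for d=0.40, with 80% power at d=0.48 or 0.42. Give the range: 57–68% at a correlation of .30, about 72–82% at .60, and t-based 80% only near .70. State how the 3.75 was obtained. In the Abstract, stop calling 180 the required size, or qualify it with the same power.

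Do not rescue the 80% by naming the mean of posttest and 3 months as the primary endpoint. The Results section says the last follow-up data were collected in December 2018, so that would be a post hoc change. It would also attach a d specified at 3 months to a different quantity.

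The cost is wording and a less favourable stated power. No pupils, visits or analyses change.

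### Intention-to-treat is given as the reason for a zero dropout allowance, but it does not restore missing follow-up outcomes, so 180 adolescents give 80% power only if follow-up is nearly complete

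*Protocol article*

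**What the plan says.** The Sample Size section sets the target at the first assessment after posttest: "The sample size was based on the expected difference (Cohen *d*=0.40) between the intervention and control condition for mental health literacy and stigma at 3-months". It assumes baseline-adjusted regression with alpha .05 and beta .20. On correlations it says: "Our provisional estimates for the correlations between pre- and posttest and between posttest and 3-months follow-up are .50". Mean class size is 18 with a coefficient of variation of .19, and "an intracluster correlation coefficient of .02 [23] lead to a design effect of 1.35". This leads to 3.75 classes per condition, rounded up to four. One more class per condition is added for the t distribution, giving five classes (90 adolescents) per condition and 180 in total. The section closes with the dropout sentence: "Since we will perform the analyses according to the intention-to-treat principle, dropout was not taken into account". No expected attrition rate is given.

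The Statistical Analyses section explains intention-to-treat as "meaning we will include all children who filled in the pretest questionnaires in the analyses to test the study hypotheses". On software it says "We will use Mplus version 8", chosen partly for its missing-data features and its handling of clustering. The tests at 3 and 6 months are described only as regression analyses. The Results section reports 185 adolescents at pretest in 10 classes, with the last follow-up collected in December 2018.

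**The concern.** The dropout sentence draws a conclusion that its premise does not support. Keeping every child with a pretest in the analysis set preserves the randomised comparison, but the information about a 3-month effect comes from outcomes observed after pretest. A child with a pretest and nothing later adds almost nothing to that effect, whatever the analysis set is called. Missing-data estimation can recover part of what is lost when a child has some later measurement; at correlations of .50 it cannot recover all of it.

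Attrition is plausible here. There are four web questionnaires running to 6 months after the program, some completed at home, and consent can be withdrawn at any time. What is at stake is the reading of the result: a null finding would be judged against a nominal 80% that the trial may not have had. The sentence also suggests that the analysis set already takes care of missing data, which may discourage a model that uses all follow-ups.

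**Working it through.** **Inputs.** From Sample Size: d = 0.40, alpha .05 (sidedness not stated; two-sided reproduces the plan's figure), power .80, correlations .50, mean class size 18, coefficient of variation .19, ICC .02, five classes per condition. From Results: 185 enrolled in 10 classes. Assumed here: every attrition rate *a*.

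**1. The plan's own figure.**
- Design effect = 1 + ((0.19² + 1) × 18 − 1) × 0.02 = 1.353, matching the stated 1.35.
- Variance factor for the mean of two post measures adjusted for one baseline, all correlations .50: (1 + 0.50)/2 − 0.50² = 0.50.
- n per arm = 2 × 0.50 × ((1.960 + 0.842)/0.40)² = 49.06, so 50.
- Classes per arm = 50 × 1.35/18 = 3.75. Round to 4, add 1, giving 5 classes, 90 per arm, 180 in total.

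The figure reproduces exactly with zero dropout. The factor 0.50 is not stated; it is inferred because it returns 3.75. A single baseline-adjusted follow-up (factor 1 − 0.50² = 0.75) gives 74 × 1.35/18 = 5.55 classes, and no baseline adjustment gives 99 × 1.35/18 = 7.43.

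**2. Power when children are lost entirely.** Remaining class size m = 18(1 − a); DE = 1 + (1.0361m − 1) × 0.02; SE = √(2 × 0.50 × DE/(5m)); noncentrality = 0.40/SE; noncentral t with 2 × (5 − 1) = 8 df, two-sided critical value 2.306.

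| Loss (assumed) | m | DE | SE | 0.40/SE | Power |
|---|---|---|---|---|---|
| 0% | 18.0 | 1.353 | 0.1226 | 3.26 | 81.4% |
| 5% | 17.1 | 1.334 | 0.1249 | 3.20 | 80.0% |
| 10% | 16.2 | 1.316 | 0.1274 | 3.14 | 78.5% |
| 20% | 14.4 | 1.278 | 0.1332 | 3.00 | 74.9% |
| 30% | 12.6 | 1.241 | 0.1404 | 2.85 | 70.5% |

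The break-even for 80% is about 5% loss.

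**3. The 185 enrolled.** With 185/10 = 18.5 per class, the same formulas give 82.2%, 79.3% and 75.7% at 0%, 10% and 20%.

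**4. Power when posttest is kept and only the 3-month outcome is lost.** Assume a common effect at posttest and 3 months. Information per child is 1/0.50 = 2 with both measures and 1/0.75 = 1.333 with posttest only. The effective factor is F = 1/(2(1 − a) + 1.333a), that is 0.517, 0.536 and 0.556 at 10%, 20% and 30%. With SE = √(2 × F × 1.353/90) and 8 df, power is 80.2%, 78.8% and 77.3%.

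**5. What an allowance would have required.** Under the plan's own recipe, 50/(1 − a) × 1.35/18 = 4.17 classes at 10% and 4.69 at 20%. Both round to 5, plus 1 for the t distribution, giving 6 classes per arm: 2 × 6 × 18 = 216 instead of 180.

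**The case against.** The strongest reply is that the missing-data model is not fully described in the article. A reader might infer that 3- and 6-month outcomes are regressed separately on condition and baseline, so that the analysis amounts to complete cases and the promise to include every child is empty. The documents do not support that. The Statistical Analyses section never says the regressions are separate, it points to the missing-data features of Mplus, and nothing rules out a joint model or earlier waves as auxiliary variables. A protocol article may leave such detail to a fuller document. This objection stands, and it is why step 2 is the pessimistic end and step 4 is shown beside it.

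A reader might also take the single-follow-up factor of 0.75 and report power of 64.7% at no loss and 57.7% at 20%. Most of that shortfall is already there at zero dropout. It comes from the variance factor, which is a separate question, and should not be counted as an effect of attrition.

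Nor do the documents show that power falls short at any realistic attrition, or that attrition is certain. No rate is given, reminders and payment for questionnaires are described, and 185 were enrolled rather than 180.

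One could argue that the fifth class per arm is a hidden reserve: under a normal approximation, 180 would hold 80% up to about 26% loss (design effect fixed at 1.35) or 33% (recomputed). But the plan says this class was added for the t distribution, so it cannot also be the dropout allowance.

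Finally, data collection is finished, no sample-size decision remains open, and confidence intervals are promised, which will show the precision achieved. That lowers the severity but does not make the rationale correct.

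**Conclusion.** The rationale is wrong as written: intention-to-treat is not a reason to set dropout to zero. The size is moderate. Relative to complete data, entire loss of children costs about 3 points of power at 10% and 6.5 points at 20%; if posttest is retained under a common effect, the cost is about 1 and 2.6 points. These figures rest on the inferred variance factor, two-sided testing, 8 degrees of freedom, loss spread evenly over classes, and assumed attrition rates. The sentence itself does not show bias or an inflated type I error; whether missing data could bias the estimates depends on a model that the article does not specify.

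**What to change.** In Sample Size, delete the clause that derives the zero allowance from intention-to-treat. State plainly that no attrition allowance was made, and restate power, or the detectable effect, at the attrition actually observed. No further enrolment is involved.

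In Statistical Analyses, if the 3- and 6-month outcomes would otherwise be regressed only on condition and baseline, fit T2, T3 and T4 jointly in Mplus with condition-by-time, the T1 outcome and class clustering. Use T3 and T4 only for the behavioural outcomes, which are not assessed at posttest. Children with any follow-up then contribute, and the missing-at-random assumption conditions on their earlier follow-up responses.

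The cost is a slightly lower stated power and a little more analysis work in software already chosen.
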